## Abstract

**Introduction::**

Fibromyalgia (FM) is a chronic condition characterized by chronic pain, fatigue and loss of function which significantly impairs quality of life. Although treatment of FM remains disputed, some studies point at the efficacy of interdisciplinary therapy. This study aims to analyze the effectiveness, cost-utility and benefits of a multicomponent therapy on quality of life (main variable), functional impact, mood and pain in people suffering from FM that attend primary care centers (PCCs) of the Catalan Institute of Health (ICS).

**Methods and analysis::**

A 2-phase, mixed methods study has been designed following Medical Research Council guidance. Phase 1: Pragmatic randomized clinical trial with patients diagnosed with FM that attend one of the 11 PCCs of the ICS *Gerència Territorial Terres de l’Ebre*. We estimate a total sample of 336 patients. The control group will receive usual clinical care, while the multicomponent therapy group (MT group) will receive usual clinical care plus group therapy (consisting of health education, exercise and cognitive-behavioural therapy) during 12 weeks in 2-hourly weekly sessions. Analysis: the standardized mean response and the standardized effect size will be assessed at 3, 9, and 15 months after the beginning of the study using multiple linear regression models. Utility measurements will be used for the economic analysis. Phase 2: Qualitative socio constructivist study to evaluate the intervention according to the results obtained and the opinions and experiences of participants (patients and professionals). We will use theoretical sampling, with 2 discussion groups of participants in the multicomponent therapy and 2 discussion groups of professionals of different PCCs. A thematic content analysis will be carried out.

**Ethics and dissemination::**

This study protocol has been approved by the Clinical Research Ethics Committee of the *Fundació Institut Universitari per a la recerca a l’Atenció Primària de Salut Jordi Gol i Gurina* (code P18/068). Articles will be published in international, peer-reviewed scientific journals.

**Trial registration::**

Clinical-Trials.gov: NCT04049006.

## Introduction

1

Fibromyalgia (FM) is a disease characterized by chronic pain, fatigue, and loss of function, which physically limits the patient and consequently impacts mood, the social and working environments, generates sleep disturbances and generally impairs quality of life.^[1]^ FM is classified as a central sensitivity syndrome (CSS), and is frequently associated to other CSS such as Chronic Fatigue Syndrome and Multiple Chemical Sensitivity.^[2,3]^

The diagnosis of FM is based on clinical criteria, initially defined by the American College of Rheumatology.^[4,5]^ New amendments added in 2016 improve the detection of the disease in the primary care (PC) setting, although at the cost of lower specificity.^[6]^ Prevalence of FM in the general population ranges between 0.2% and 6.6%, and in women from 2.4% to 6.8%.^[7]^ In Spain, prevalence is estimated at 2.45% ([name], personal communication, July 2019), with a female/male ratio of 21:1, and is usually diagnosed in middle-aged people.^[1,8]^

The cost of FM for the health system is high.^[9]^ Total annual costs per patient in industrialized countries are estimated between 7256 and 7900 euros, and indirect costs (for instance, productivity loss) are considered higher than direct costs (such as medical visits and multiple prescriptions).^[10–12]^ In addition, when comparing with other conditions that cause chronic pain, FM is associated with higher rates of unemployment and a higher number of sick leave days.^[13]^

The best treatment for FM is currently disputed. Some studies have shown clinical improvement with non-pharmacological therapies, particularly with exercise^[14]^ and with cognitive-behavioral therapy (CBT).^[15,16]^ There is also some evidence on the effectiveness of multicomponent group therapy, which involves patient education, exercise and CBT^[17,18]^, with reported clinical improvement that lasts 3 to 12 months after the intervention.^[19,20]^ Interdisciplinary interventions conducted from hospitals^[21–23]^ and PC^[24–27]^ have obtained similar positive results. The most recent review (2017) of the European League Against Rheumatism (EULAR)^[28]^ on the management of FM endorsed the abovementioned therapies, and also included promising results on complementary therapies such as mindfulness, hydrotherapy and acupuncture. There is also evidence on the benefits of some drugs for the treatment of severe pain and insomnia (amitriptyline and cyclobenzaprine, duloxetine and pregabalin).^[28]^

Few studies on the economic evaluation of interventions for patients with FM have been published to date.^[29–33]^ With respect to cost-utility, psychology-based therapies showed better results in most studies.^[30–33]^ A cost-utility study carried out in Spain that compared a psychoeducational intervention with usual clinical care found that on average, the incremental gain in quality-adjusted life years (QALYs) per person was 0.12 (0.06 to 0.19).^[30]^

Complex interventions, as well as interventions based on Health Coaching, aim to promote healthy habits. The design of complex, multimodal, and interdisciplinary interventions aims to achieve a better implementation of interventions adapted to the people and their environment, and greater sustainability. The Medical Research Council has established a methodology to develop this type of interventions, which comprise various phases that are implemented iteratively using both quantitative and qualitative methodologies. The combination of methodologies incorporates the input of patients, in order to better adapt the intervention to their needs, and takes into account the characteristics (social, resources, health etc.) of the environment where the intervention takes place.^[34–36]^

In 2016, 18 accredited units specialized in Central Sensitivity Syndromes (USCSS) were created throughout Catalonia,^[37]^ with the aim to provide consistent health care to all patients with fibromyalgia.^[38]^ The USCSS consist of interdisciplinary teams based both in primary care centers (PCCs) and in hospitals.

After reviewing the available evidence, we want to propose a therapy for patients with FM to be delivered within the primary health care system. The objective of this proposal is to analyze the effectiveness and cost-utility of a multicomponent therapy that consists of health education, exercise and cognitive-behavioral therapy, and to compare it with usual clinical care with regard to quality of life, functional impact, mood and pain in patients with FM that attend Primary Health Care Centers (PCCs) of the *Gerència Territorial Terres de L’Ebre* of the Catalan Institute of Health (ICS). Based on the data collected about the opinion and experience of patients and professionals, the following aspects of the implementation of the intervention will also be evaluated: acceptability, adaptability, adherence, feasibility and compatibility. This intervention is founded on the transtheoretical model of change, which can be applied to multiple behaviors and risk factors and is recommended in research with a multibehavioral or multiple risk approach. Furthermore, the intervention applies the conceptual framework of the “5As” (Assess, Advise, Agree, Assist, and Arrange-follow up) to standardize and facilitate the intervention.^[39,40]^

## Methods and design

2

### Setting and participants

2.1

Participants will be patients diagnosed with FM that attend 11 PCCs of the ICS *Gerència Territorial Terres de l’Ebre*.

#### Inclusion criteria (all criteria must be met)

2.1.1

Clinical diagnosis of FM (International Classification of Diseases-10 codes: M79.0, M79.7);Having a phone number;Accepting participation in the study.

#### Exclusion criteria

2.1.2

Active psychotic episode;Intellectual impairment;Severe depression and personality disorder;Auto/heteroaggressive behaviour;Self-reported use of psychoactive substances;Having previously participated in a multicomponent therapy group (MT group) in the *Terres de l’Ebre* (pilot study);Unable to attend the group sessions.

### Training of FM specialists

2.2

Before starting the study, a nurse or a general practitioner of each PCC (hereafter called “FM specialists”) will receive training on aspects related to FM, exercise, cognitive-behavioral therapy and on the methodology of data collection for the study. To guarantee quality and consistency, annual refresher training will be provided.

Following Medical Research Council guidelines^[35]^ on the evaluation of complex interventions, we will conduct a mixed methods study consisting of 2 phases. Figure 1 shows the study flowchart.

**Figure 1 F1:**
[figure not shown]
Flowdiagram of the study. FIQR = Revised Fibromyalgia Impact Questionnaire, HADS = Hospital Anxiety and Depression Scale, MT group = multicomponent therapy group, SF-36 = Short Form 36 health survey questionnaire, VAS = visual analog scale.

### Phase 1: Study of the effectiveness and cost-utility of the intervention

2.3

#### Study design and sample size

2.3.1

We will carry out a pragmatic randomized clinical trial (type: parallel group) with patients suffering from FM to compare the effect of a multicomponent therapy with usual clinical care in PC. The intervention will be structured in study units. Each study unit consists of a MT group and a control group, each with 10 to 12 participants. Assuming an alpha error of 0.05 and a beta error of 0.05 in a bilateral contrast, and an estimated dropout rate of 20%, a sample size of 130 participants in each group of the study will be required in order to detect a score difference equal or higher than 5 units in the Short Form 36 (SF-36) health survey questionnaire. A common standard deviation of 10 is assumed. Based on these calculations, we will create a total of 14 MT groups, with their respective control groups, between April and December 2019. The number of participants estimated is 336 patients.

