#### Randomization, recruitment, and data collection

2.3.2

For each study unit a randomization list will be generated according to Efron procedure,^[41]^ using the IBM SPSS Statistics v.23.0. package for Windows. An appointment will be arranged with patients who meet inclusion criteria for the first interview, where they will receive the information leaflet of the study and will sign the informed consent form. Next, patients will be allocated to a study group according to the randomization list. Additionally, the patients will be asked to respond to the study questionnaires (SF-36v2 health survey questionnaire^[42]^ (Optum, Inc. license number QM048943), Revised Fibromyalgia Impact Questionnaire (FIQR),^[43,44]^ Visual Analog Scale (VAS),^[45,46]^ tender points^[47]^ and Hospital Anxiety and Depression Scale (HADS)^[48,49]^) and will take part in the activities planned for each group (see below).

Control group: Patients in the control group will receive regular clinical care in their PCC,^[50]^ which consists on an individual visit with the FM specialist, who will conduct a standardized clinical history and will inform the patient on the disease using a custom designed leaflet.

MT group: in addition to usual PC clinical care, participants will receive MT consisting of health education, exercise and cognitive-behavioural therapy, during 12 weeks in 2-hourly weekly sessions (Fig. 2). Group therapy will be delivered by the FM specialist in each PCC, with the support of the physiotherapist and the psychologist of the USCSS.

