#### Statistical analysis

2.3.5

Data analysis will take place at baseline and after 3, 9, and 15 months. Intention to treat analysis will be used. The quality of data collection will be periodically monitored to minimize biases due to incomplete data. The non-response bias will be evaluated at all points of follow up. Descriptive analyses of variables will be carried out using the media (standard deviation), median (interquartile range) or frequency (percentage), depending on the distribution of variables.

For comparisons between and within the 2 study groups (intervention and control) and the study variables, the following tests will be used: Student's *t* test for independent or paired data, McNemar, Chi-square test and analysis of variance or the corresponding non-parametric tests.

To evaluate the effectiveness of the intervention at each point of follow up, we will calculate the change in scores of the SF-36 and the other questionnaires in the intervention group minus the change in the control group, and the standardized effect size (SES). The SES will be calculated as the difference of the mean of the scores of both groups divided by the combined standard deviation. To detect differences within each study group, the difference of the means between baseline and each follow up point will be calculated, and also the effect size or standardized mean response (SMR), in accordance with Kazis’ method.^[52]^ The SMR will be calculated as the mean change divided by the standard deviation of change. To evaluate the SMR and the SES we will use Cohen rule, which classifies effect size as small (0.2 to 0.5), medium (0.5 to 0.8), and large (greater than 0.8).

Finally, multiple linear regression models will be used to explore the variables associated with the percentage change [(follow-up scores minus baseline scores)/baseline scores × 100] of the scores in the SF-36 and other questionnaires. The multivariate models will include variables that might be clinically linked, and the variables statistically significant in the previous bivariate analyses. Models will be also adjusted by confounding variables. Interactions and collinearity will be evaluated.^[53]^ Statistical significance for all study tests will be set at α ≤ 0.05 and 95% CI. The statistical package IBM SPSS Statistics v.23.0.for Windows will be used.

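### Only the therapy arm is treated in groups, but the sample size and the named tests treat all patients as independent. Standard errors may be too small, while power at the planned 336 survives modest clustering.

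*Protocol article*

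**What the plan says.** **Design.** Under Study design and sample size, the protocol article organises the trial in study units: "Each study unit consists of a MT group and a control group, each with 10 to 12 participants". It plans 14 MT groups with their control groups, 336 patients in all. Under Randomization, recruitment, and data collection, each unit has its own randomisation list and patients are allocated individually from it. The MT arm then has 12 weekly two-hour sessions: "Group therapy will be delivered by the FM specialist in each PCC". Control patients have an individual visit with the same kind of specialist and no group sessions.

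**Sample size.** The target is to "detect a score difference equal or higher than 5 units in the Short Form 36 (SF-36) health survey questionnaire", with two-sided alpha 0.05, beta 0.05 and 20% dropout. "A common standard deviation of 10 is assumed". The result is that "a sample size of 130 participants in each group of the study will be required". No ICC or design effect appears.

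**Analysis.** Under Statistical analysis: "For comparisons between and within the 2 study groups (intervention and control) and the study variables, the following tests will be used". The list that follows is Student's t test, McNemar, chi-square, and analysis of variance or non-parametric equivalents. Multiple linear regression is added to explore percentage change. No term for therapy group, study unit or centre is named, nor any random effect or cluster-robust error.

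**The concern.** Patients in one MT group share a leader, the other members and 12 weeks of sessions, so their outcomes can be more alike than those of patients in different groups. Controls have no such shared treatment. This is a partially nested design: individual randomisation, with clustering created by treatment in one arm only.

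A t test or ordinary regression counts each MT patient as a full independent observation. If MT groups differ from one another for reasons that controls in the same unit do not share, the variance of the MT mean is larger than such a test assumes. The main effectiveness comparison then has a confidence interval that is too narrow and a type I error above 5%. Recruiting more groups of the same size does not cure this, because the inflation depends on group size and ICC. The 95% power attached to 130 per arm also rests on zero correlation.

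**Working it through.** **Inputs from the article:** difference 5, SD 10, alpha 0.05 two-sided, beta 0.05, dropout 20%, MT groups of 10 to 12, 14 MT groups, 336 patients.

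**Assumed, not in the documents:** an extra MT-group ICC of 0.01, 0.05 or 0.10.

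**1. Reproduce the plan's figure.** n = 2(1.96 + 1.645)² × 10² / 5² = 103.96, so 104 evaluable per arm; 104 / 0.8 = 130. The match is exact, so the 130 contains no allowance for clustering.

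**2. Planned size.** 336 = 14 × 2 × 12, or 168 per arm. After 20% dropout this is 134.4 completers per arm and m = 12 × 0.8 = 9.6 per MT group.

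**3. Standard error and type I error, no shared unit variance.** With n completers per arm:
- design effect in the MT arm: DE = 1 + (m − 1) × ICC
- true SE = 10 × √((1 + DE)/n); naive SE = 10 × √(2/n); ratio = √((1 + DE)/2)
- type I error = 2Φ(−1.96/ratio)

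| ICC | DE | SE ratio | Type I error |
|---|---|---|---|
| 0.01 | 1.086 | 1.02 | 5.5% |
| 0.05 | 1.43 | 1.10 | 7.5% |
| 0.10 | 1.86 | 1.20 | 10.1% |

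**4. Power,** Φ(5/SE − 1.96), normal approximation, with the true SE:

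| ICC | 130 per arm (11 groups, 104 completers) | 336 planned (groups of 12) | All groups of 10 (280 patients, m = 8) |
|---|---|---|---|
| 0 | 95.0% | 98.4% | 96.3% |
| 0.01 | 94.2% | 98.0% | 95.7% |
| 0.05 | 90.6% | 96.1% | 93.2% |
| 0.10 | 85.6% | 92.9% | 89.6% |

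With groups of 12, power stays at 95% or more up to an ICC of about 0.068, or about 0.052 with a t reference on Satterthwaite degrees of freedom. If every group holds 10, the limit is about 0.022, or about 0.009 with the t reference.

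**5. Effect of variance shared by both arms of a unit.** Let u be the unit variance common to both arms and g the extra MT-group variance, each as a fraction of the total. The shared part cancels from the difference between arms, but an unadjusted t test still counts it as noise. Then true/naive variance = 1 + [(m − 1)g − 2u]/2. The naive test is anti-conservative only if 8.6g > 2u, that is, if u is below about 4.3 times g. For u + g = 0.05:
- all extra (u = 0, g = 0.05): ratio 1.215, type I error 7.5%
- half shared (u = g = 0.025): ratio 1.0825, type I error 6.0%
- four-fifths shared (u = 0.04, g = 0.01): ratio 1.003, type I error 5.0%
- all shared (u = 0.05, g = 0): ratio 0.95, type I error 4.4%

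**The case against.** **Power.** A reader might infer that the trial's 95% power fails. The documents do not support that at the size planned. The article requires 130 per arm but plans 168, and the surplus carries power past 95% over much of the assumed range. This stands. The article does not present the surplus as a clustering allowance, and groups of 10 would use up most of it.

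**Inflation.** A reader might also take a type I error above 5% as established. It is not. The ICC is unknown, randomisation is within unit, and controls see the FM specialist too, so part of any leader or centre effect is common to both arms. Step 5 shows that this can reduce or reverse the inflation. This stands as a limit on size. On the other side, the article's effectiveness measure is change from baseline. That removes stable differences between units and so tends to shrink u, while differences that arise during therapy remain in g.

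**Mitigation.** The Discussion promises standardised content, trained leaders and the same three professional roles in each unit. These can lower the ICC, but they do not make it zero.

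**Choice of model.** There are 11 centres for 14 groups, so some leaders may run more than one group. Controls are also invited to the next MT group in their centre (Ethics and dissemination), so a random effect confined to the MT arm may not describe later visits fully. Both points call for a sensitivity analysis; neither justifies ignoring the grouping.

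**Scope.** The full protocol or SAP is not shown and may specify a clustered model. An ICC or a degrees-of-freedom method could properly be left to it. The article, however, itself names tests for independent patients and gives a sample size that depends on independence.

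**Conclusion.** The point holds in limited form. The design groups patients by treatment in one arm, and the stated sample size and tests take no account of it.

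- **Validity of the main comparison.** If MT-group correlation exceeds what units share across arms, standard errors are too small. The understatement (SE ratio 1.02 to 1.20, type I error 5.5% to 10%) applies to assumed ICCs of 0.01 to 0.10 with 9.6 completers per group and no shared unit variance. Shared variance lowers these figures, and above about 4.3 times the MT-group variance it removes the inflation.
- **Power.** The 95% for 130 per arm is exact only at zero ICC. At the planned 336 it survives to an ICC of about 0.05 to 0.07 with groups of 12, and to about 0.02 (normal approximation) if all groups hold 10. Power is the secondary issue.

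**What to change.** **Analysis.** Make the effectiveness analysis a linear mixed model with arm, baseline score, study unit and a random MT-group effect present only in the MT arm, using Satterthwaite or Kenward-Roger degrees of freedom. The unit term takes out the variance shared by both arms and the MT-group term carries the extra clustering; the named tests do neither. Add a sensitivity analysis with clustering at centre or leader level.

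**Sample size.** Replace the unqualified 95% at 130 per arm with power for 336 patients over a stated range of MT-group ICCs, and show the case of groups of 10.

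**Cost.** A change of wording and model specification, with no extra patients. Intervals will be slightly wider if clustering is present, and the stated power slightly less favourable. Unit membership follows from the per-unit randomisation lists, but the sponsor should confirm that both unit and group membership are kept in the analysis dataset.

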#### Randomization, recruitment, and data collection

2.3.2

For each study unit a randomization list will be generated according to Efron procedure,^[41]^ using the IBM SPSS Statistics v.23.0. package for Windows. An appointment will be arranged with patients who meet inclusion criteria for the first interview, where they will receive the information leaflet of the study and will sign the informed consent form. Next, patients will be allocated to a study group according to the randomization list. Additionally, the patients will be asked to respond to the study questionnaires (SF-36v2 health survey questionnaire^[42]^ (Optum, Inc. license number QM048943), Revised Fibromyalgia Impact Questionnaire (FIQR),^[43,44]^ Visual Analog Scale (VAS),^[45,46]^ tender points^[47]^ and Hospital Anxiety and Depression Scale (HADS)^[48,49]^) and will take part in the activities planned for each group (see below).

Control group: Patients in the control group will receive regular clinical care in their PCC,^[50]^ which consists on an individual visit with the FM specialist, who will conduct a standardized clinical history and will inform the patient on the disease using a custom designed leaflet.

MT group: in addition to usual PC clinical care, participants will receive MT consisting of health education, exercise and cognitive-behavioural therapy, during 12 weeks in 2-hourly weekly sessions (Fig. 2). Group therapy will be delivered by the FM specialist in each PCC, with the support of the physiotherapist and the psychologist of the USCSS.

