#### Masking

2.3.3

Due to the study characteristics (pragmatic trial), it is not possible to mask the health professionals and participants. The data analyst will be blind to the patients’ allocation group.

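### Separate Efron lists for each small unit, in an open trial with one specialist serving both arms, leave the next allocation moderately guessable; randomising each assembled unit in one step removes this

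*Protocol article*

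**What the plan says.** All references are to the protocol article.

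- **Method and level** (2.3.2): "For each study unit a randomization list will be generated according to Efron procedure". The coin probability is not given.
- **Order of events** (2.3.2): an appointment is made for a first interview, the patient is informed and signs consent, and then: "Next, patients will be allocated to a study group according to the randomization list". The study questionnaires are mentioned after that step.
- **Unit size** (2.3.1): "Each study unit consists of a MT group and a control group, each with 10 to 12 participants". For the whole trial, "we will create a total of 14 MT groups, with their respective control groups", with 336 patients expected.
- **Centres** (2.1): "patients diagnosed with FM that attend 11 PCCs".
- **Contact with both arms** (2.3.2): control care is described as care "which consists on an individual visit with the FM specialist". For the other arm, "Group therapy will be delivered by the FM specialist in each PCC". The Discussion gives each unit three professionals, one of them the FM specialist of the centre.
- **Masking** (2.3.3): "it is not possible to mask the health professionals and participants". Only the data analyst is blind.

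The article does not say who conducts the first interview, who judges eligibility, who holds the list, or whether a unit's patients are allocated singly or together.

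**The concern.** Under Efron's rule the next patient goes to the under-represented arm with a probability above one half, so whoever knows the current counts knows the more likely next arm. Three features that the article does fix make those counts easy to know: the list restarts for every unit of 20 to 24 patients, nothing is masked at the centre, and one specialist has contact with both arms of the unit. Hiding the list does not help, because the information is in the tally.

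If someone with that knowledge could influence who is interviewed next or who counts as eligible, patients expected to do well could be entered when the therapy arm is due. Some exclusion criteria in 2.1.2 leave room for judgement, for example ability to attend the sessions. The arms would then differ before treatment, and both the SF-36 comparison and the cost-utility comparison would carry that difference.

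There is also a practical mismatch. Efron's coin does not guarantee equal arms, yet the plan counts on groups of 10 to 12 in both arms of every unit.

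**Working it through.** **Inputs from 2.3.1:** alpha 0.05 two-sided, beta 0.05, difference 5, SD 10, dropout 20%, 14 units, 10 to 12 patients per arm per unit, 336 patients.
**Assumption:** coin probability p = 2/3, range 0.60 to 0.75.

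**1. The plan's own figures.** n = 2(1.960 + 1.645)² × 10² / 5² = 103.96, so 104 per arm. Then 104 / 0.80 = 130, as stated. Also 336 / 14 = 24, so the target assumes 12 + 12 in every unit.

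**2. Guess rate.** Let D be the difference in arm counts before an allocation. The lagging arm is drawn with probability p if D ≠ 0, and each arm with 1/2 if D = 0. Someone who always guesses the lagging arm is therefore right with probability 1/2 + (p − 1/2) × P(D ≠ 0). P(D ≠ 0) comes from an exact recursion over the arm counts, averaged over the unit.

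For 24 patients and p = 2/3, 71.0% of allocations are made under imbalance: 0.5 + (1/6) × 0.710 = 0.618.

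| p | correct guesses of 24 | rate | excess over 12 |
|---|---|---|---|
| 0.60 | 13.83 | 57.6% | 1.83 |
| 2/3 | 14.84 | 61.8% | 2.84 |
| 0.75 | 15.88 | 66.1% | 3.88 |

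A 20-patient unit at p = 2/3 gives 61.7%, so unit size hardly matters.

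**3. Balance within a unit, no cap.** For 24 patients, the probability of ending at exactly 12 + 12 is 0.361, 0.505 and 0.667 for p = 0.60, 2/3 and 0.75. So about 64%, 49% and 33% of units end unequal, and every unequal 24-patient unit has an arm above 12. A 20-patient unit is unequal about as often (49% at p = 2/3), which puts one arm below 10. With 22 patients there is slack: an arm exceeds 12 in 1 − 0.884 = 12% of units at p = 2/3.

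**4. Alternatives on the same measure.** Sequential permuted blocks within a unit are more guessable: 75% for blocks of 2 and 70.8% for blocks of 4. If the whole unit is enrolled before anyone in it is allocated, there is no tally to use at enrolment and the rate is 50%.

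**5. Upper-bound illustration in SF-36 points.** If every guess were acted on, the between-arm bias would be about (2 × 0.618 − 1) × Δ = 0.24Δ. Here Δ is the difference in expected outcome between favoured and unfavoured patients. The documents give no Δ. Assumed values of 2.5, 5 and 10 points give about 0.6, 1.2 and 2.4 points, against the 5-point target. With 104 per arm and SD 10, a bias of 1 point would raise the two-sided 5% error to about 11%, and a bias of 0.5 point to about 6.5%.

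**The case against.** The strongest reply is that the step from a guessable sequence to steered enrolment is not in the document. One-at-a-time allocation is inferred from individual interviews followed by allocation. No sentence puts the specialist in charge of invitation or eligibility; section 2.2 says only that specialists are trained in data collection, among other things. A condensed article may leave these operations to the full protocol. All of this stands, and it is why the risk is put conditionally and why missing concealment detail is not counted as an error.

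Other parts of the reply also stand:

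- Efron's coin is not a poor choice among sequential methods. At about 62% it is less guessable than small permuted blocks.
- A reader might infer that 12 per arm is a hard ceiling, so that the last places in a unit are certain (about 1.9 per 24-patient unit at p = 2/3, with a guess rate of 64.5%). The article gives 10 to 12 as a planned size and states no cap.
- A reader might take the SF-36 figures as an expected bias. They assume an invented Δ and full steering at every imbalanced allocation in every unit.
- A reader might conclude that such bias could be neither seen nor reduced. Section 2.3.5 compares change between the arms and mentions adjustment for confounders, so differences in measured severity would be partly visible and partly removed. Unmeasured traits such as motivation would not.
- Section 2.5 promises controls an invitation to the next therapy group at their centre, which weakens the motive to steer.

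What the reply does not answer is that the tally remains informative however well the list is concealed, and that a simpler scheme fits this design better.

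**Conclusion.** The point holds as a moderate, conditional weakness of the stated method. The article fixes the per-unit Efron lists, the small units, the open design and the specialist's contact with both arms. Given sequential allocation and an informed person with influence on enrolment, the next arm can be guessed about 62% of the time instead of 50%, or roughly 2.8 extra correct guesses per 24-patient unit. This rests on the assumed p = 2/3; the range is 58% to 66% for p from 0.60 to 0.75.

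Separately, and needing neither of those conditions, uncapped Efron would miss 12 + 12 in about 49% of 24-patient units (33% to 64%), in conflict with the group sizes on which the total of 336 is built.

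The documents do not show that enrolment will be steered, and they support no estimate of resulting bias. The change is still worth making, because it removes the problem at very little cost.

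**What to change.** In 2.3.2, replace allocation from a per-unit Efron list with allocation of the whole unit in one step:

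1. Obtain consent, confirm eligibility and complete the baseline questionnaires for all patients of a unit.
2. Have a study team member outside the primary care centre run a single random 1:1 permutation of that unit's members, in the SPSS package already named.
3. Release the allocation to the centre before the therapy starts.

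No patient can then be enrolled with a better than even guess of the arm. A unit with an even number of patients is split equally by construction, so 24 gives 12 + 12. Baseline scores are also clearly collected before the arm is known.

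Permuted blocks of varying size within a unit should not be used as a substitute. Guessing the lagging arm needs no knowledge of block size, and this route is no less predictable than Efron.

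Cost: a wording change and a different order of work, with no extra patients or visits. The earliest patients in a unit wait to learn their arm, and controls wait for their individual visit. Therapy patients would largely wait in any case, because a group has to be assembled before its sessions begin.
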